# Feasibility of a physical activity programme embedded into the daily lives of older adults living in nursing homes: protocol for a randomised controlled pilot feasibility study

**DOI:** 10.1186/s13063-018-2848-4

**Published:** 2018-08-29

**Keywords:** Physical activity, Nursing home, Feasibility, Older adults, Qualitative, Economic

## Abstract

**Background:**

Older adults living in nursing homes spend the majority of their time inactive. The associated levels of chronic disease place an increasing burden on healthcare systems. Physical activity (PA) interventions delivered through exercise classes may be resource-intensive and require specialist staff. The aim of this study is to explore the feasibility and acceptability of a PA programme embedded into the daily lives of older adults living in nursing homes and to examine the preliminary effects of this on physical mobility and quality of life.

**Methods:**

A randomised controlled pilot feasibility study, including embedded qualitative and economic components will be carried out. Two randomly selected nursing homes will take part in the study; participants (*n* = 20) in one nursing home will receive a three-month PA intervention and participants (n = 20) in the other will be a usual care control. Nursing home staff will be provided with training and support to monitor participants PA programmes. Feasibility data will be collected on recruitment, randomisation, assessment and intervention procedures. Criteria for progression of the pilot feasibility study to a definitive trial will be specified. The Timed Up and Go test, Nottingham Health Profile, 10-Metre Walk test, the Investigating Choice Experiments for the Preferences of Older People Capability index and the Bangor Goal Setting Interview will be assessed at baseline, three-month and 12-month follow-up. Between-group and within-individual effects will be estimated using appropriate linear mixed models. Semi-structured interviews will be conducted with staff and participants of the intervention group within one month after the intervention to explore the feasibility and acceptability of the programme. A subset of control participants will be interviewed to describe usual care. Economic data will be collected to examine costs of the intervention in comparison with costs in the control group.

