## Methods

### Design and setting

A randomised controlled pilot feasibility study, with embedded qualitative and economic components, will be carried out. Two nursing homes will take part in the study; participants in one nursing home will receive the PA intervention and participants in the other will receive usual care. In order to avoid contamination between intervention and control groups, randomisation will take place at nursing home level [12]. The pilot feasibility study will not be an exact scale model of a definitive RCT, the difference being that follow-up outcome assessment will not be blinded as a full analysis of outcome data is not intended. However, the recruitment, randomisation, assessment and intervention conditions will be similar to a definitive RCT in order to answer the feasibility research questions. Figure 1 provides a CONSORT flow diagram displaying the movement of participants throughout the study. A schedule for enrolment, interventions and assessments is displayed in Fig. 2. The protocol adheres to the Standard Protocol Items Recommendations for Interventional Trials (SPIRIT) guidelines (Additional file 1) [21] and the SPIRIT-Patient Reported Outcomes Extension [22].

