### Sample size calculation

An objective of this study is to assess the feasibility of recruiting and retaining the required number of participants per nursing home which would be needed in a definitive RCT. Therefore, the sample size calculation for this pilot feasibility study is based on the estimated power calculation for a definitive cluster RCT using the primary outcome measure, the Timed Up and Go (TUG) test [23]. In the absence of normative TUG data for an Irish cohort of older adults living in nursing homes, sample size calculations for a definitive RCT were estimated using a New Zealand sample of older adults living in residential care [12]. The sample size requirements for a definitive RCT were calculated as being a minimum of four clusters of size 20 in each arm, in order to have 80% power (α = 0.05) to detect a mean change in TUG score of 4.7 s (± 6.8 s). The current study will recruit one nursing home for each arm. The desired number of participants in each nursing home will be maintained as 20 in order to assess the recruitment potential, recruitment time and feasibility of delivering the intervention to this number of participants. The number of participants lost to follow-up per nursing home will be recorded to inform the final numbers needed when recruiting to the definitive RCT.

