### Statistical analysis

#### Quantitative analysis

The data analysis software SPSS Statistics (24.0 for Windows, Chicago, IL, USA) will be used to manage and analyse quantitative data. Feasibility data will be collated using descriptive statistics and, where relevant, evaluated against progression criteria. Demographical information in both groups will be tabulated and summarised. The effect of the intervention on clinical outcomes will be examined using suitable numerical and graphical summaries. The statistical analysis will serve primarily to provide an estimate of the likely effect size and variability of the response within an individual over time. This, as well as the mean and standard deviation of the primary outcome measure at baseline and the participant attrition rate, will enable a more accurate sample size calculation for a definitive RCT. All within- and between-group outcome analyses will be treated as preliminary and interpreted with caution.

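### With one nursing home per arm, the linear mixed model named in the abstract cannot give a valid standard error for the between-group effect

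*Protocol article*

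**What the plan says.** The abstract (Methods) gives the only named model for the outcome data: "Between-group and within-individual effects will be estimated using appropriate linear mixed models".

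Under Design and setting, "randomisation will take place at nursing home level", and "participants in one nursing home will receive the PA intervention and participants in the other will receive usual care". Sample size calculation repeats this: "The current study will recruit one nursing home for each arm". It also fixes the size of each home: "The desired number of participants in each nursing home will be maintained as 20".

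The Quantitative analysis section names no model. It says "The effect of the intervention on clinical outcomes will be examined using suitable numerical and graphical summaries", and adds that the analysis is mainly to estimate the likely effect size and the within-person variability over time. It treats all within-group and between-group results as preliminary. Design and setting, explaining why follow-up is unblinded, says that "a full analysis of outcome data is not intended".

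The estimate has planned uses. Table 1 lists the effect size and variance of the primary outcome, the Timed Up and Go (TUG), under a primary research question. Quantitative analysis feeds them into the definitive sample size. Health economic analysis uses TUG data as the basis of the cost-effectiveness analysis.

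**The concern.** When every intervention resident lives in one home and every control resident in the other, the arm contrast is the home contrast. A random effect for resident deals with repeated measures on the same person. It does not deal with two homes that would have drifted apart over three or twelve months for reasons unrelated to the programme, such as staffing, case mix or an outbreak of illness. A random effect for home cannot be separated from arm. A model that fits therefore treats the residents as if they had been randomised individually.

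The risk is that an ordinary difference between two homes is reported with more precision than it has. It could then be carried forward as a preliminary treatment effect into the sizing of the definitive trial and the incremental cost-effectiveness analysis. The article mentions the small number of homes as a limitation. It does not say that arm and home are confounded or that between-home variation cannot be estimated.

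**Working it through.** **Inputs.** From Sample size calculation: difference 4.7 s, 6.8 s (read as an SD), 80% power, α = 0.05 (taken as two-sided), cluster size m = 20, "a minimum of four clusters of size 20 in each arm". From Design and setting: one home per arm. Not stated: the ICC, which is an assumption below. Because the contrast of interest is in change over time, the relevant ICC is that of change; stable differences in level between homes cancel.

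**1. The plan's own figure.** Individually randomised n per arm = 2 × [6.8 × (1.96 + 0.84) / 4.7]² = 32.86, so 33. Four homes of 20 give 80 per arm, a design effect of 80 / 32.86 = 2.43. Solving 1 + 19 × ICC = 2.43 gives ICC = 0.0755. Three homes of 20 would suffice up to (60 / 32.86 − 1) / 19 = 0.043. By normal approximation, four is therefore the minimum for an ICC from about 0.043 to 0.0755. With a cluster-level t-test (6 df for four homes per arm), four is the minimum for about 0.001 to 0.036. The figure is compatible with its inputs but cannot be confirmed without the ICC. Across the two methods the compatible range is about 0.001 to 0.076.

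**2. Identifiability.** The design matrix with columns intercept, arm, home 1 and home 2 has rank 2, the same as intercept and arm alone. Two homes less two arm means leaves 0 degrees of freedom for between-home variance.

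**3. Size of the distortion.** With total SD σ = 6.8 s:

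- Model SE (sees only within-home variation) = σ × √[(2/m)(1 − ICC)]
- True SE = σ × √[(2/m)(1 + (m − 1) × ICC)]
- Ratio r = √{[1 + (m − 1) × ICC] / (1 − ICC)}, which does not depend on σ
- Coverage of a nominal 95% interval = P(|T₃₈| < 2.024 / r)

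| Assumed ICC | Model SE (s) | True SE (s) | Ratio r | Coverage |
|---|---|---|---|---|
| 0 | 2.15 | 2.15 | 1.00 | 95.0% |
| 0.01 | 2.14 | 2.35 | 1.10 | 92.7% |
| 0.02 | 2.13 | 2.53 | 1.19 | 90.4% |
| 0.05 | 2.10 | 3.00 | 1.43 | 83.4% |
| 0.075 | 2.07 | 3.35 | 1.62 | 78.1% |
| 0.10 | 2.04 | 3.66 | 1.80 | 73.4% |

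At ICC 0.05, for example, r = √(1.95 / 0.95) = 1.43. The model's 95% half-width is 4.24 s, against 5.89 s if the ICC were known. At the bottom of the compatible range, ICC 0.001, r = √(1.019 / 0.999) = 1.01.

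**4. Simulation check.** In 20,000 simulated trials per ICC with no treatment effect, change scores were compared by t-test. With two balanced time points this equals the arm-by-time test of a random-intercept model. Rejection at nominal 5% was 5.0%, 7.5%, 9.5%, 16.3%, 21.8% and 26.6% for ICC 0, 0.01, 0.02, 0.05, 0.075 and 0.10, in line with one minus the coverage above.

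**The case against.** The strongest reply is that the harm attaches to output that is not planned. That is fair as far as it goes. A reader might infer that the protocol commits to between-arm confidence intervals or significance tests. It speaks only of estimating effects, so the coverage and error rates above are conditional on an interval or test being produced.

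A reader might also infer that the abstract and the analysis section contradict each other. They do not. The analysis section refers to between-group analyses and an effect-size estimate, and a mixed model over three visits is a natural route to within-person variability. The section is silent on the model, and an article may condense. The remark that no full outcome analysis is intended explains the lack of blinding; it does not exclude estimation.

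It can be said, too, that model terms belong in an analysis plan that is not shown. That does not help here: no choice of terms recovers a variance component with 0 degrees of freedom.

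The stated caution and the acknowledged small number of homes lower the risk of misreading, but neither names the confounding nor changes a standard error.

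The consequences also have limits. The progression criteria in Table 5 rest on recruitment, timing, retention and adherence, not on any between-arm outcome. The offer of materials to the control home carries no significance criterion. The economic results are described as preliminary.

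**Conclusion.** The point holds in a limited form. The statement that between-group effects will be estimated by linear mixed models cannot deliver a valid between-group standard error in this design. Within-individual effects and within-home variability are unaffected.

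The size depends on an ICC of change that the article does not give. Over an assumed 0.01 to 0.10, the true standard error is 1.10 to 1.80 times the model's and nominal 95% coverage is about 93% down to 73%. It is tempting to read the definitive-trial calculation as implying an ICC of 0.036 to 0.076, and hence a guaranteed substantial distortion. That would join the upper limits of two different methods. The calculation is compatible with values down to about 0.001, where the distortion is negligible. That the article sizes the definitive trial as a cluster trial shows that clustering is anticipated, but not how large it is.

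The matter is worth correcting because the between-group estimate serves a primary research question, the definitive sample size and the cost-effectiveness analysis.

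**What to change.** 1. Make the abstract and the Quantitative analysis section say the same thing about the model and what it is for.
2. Use the mixed model only for within-home change over time and within-person variability.
3. State plainly that arm and home are confounded and that between-home variation cannot be estimated from these data.
4. Report the between-home difference in change descriptively, without a p-value. If an interval is shown, multiply the model variance by [1 + (m − 1) × ICC] / (1 − ICC) over a stated ICC range, such as 0.01 to 0.10, and label it as a difference between two homes.
5. Do not treat that difference as a treatment effect when sizing the definitive trial or in the cost-effectiveness analysis. Take the ICC for the definitive trial from outside this study.

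The cost is wording only: no new homes, residents or data. The downside is that the between-group result is reported as less precise.

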**Discussion:**

The findings will facilitate refinement of the PA programme and development of a clear protocol for subsequent evaluation of the PA intervention in a definitive randomised controlled trial.

**Trial registration:**

ClinicalTrials.gov, NCT03484715. Registered on 30 March 2018.

**Electronic supplementary material:**

The online version of this article (10.1186/s13063-018-2848-4) contains supplementary material, which is available to authorized users.

## Background

Globally, the number of older adults unable to live independently is forecast to quadruple by 2050 [1]. The rapid change in population demographics will make nursing homes a vital pillar of healthcare for future older generations. Physical inactivity is a global health pandemic and is one of four leading contributors to premature mortality [2]. In nursing homes, the consequences of physical inactivity are even more apparent and may manifest as pressure sores, contractures, cardiovascular deconditioning, urinary infections and increased dependency [3]. The World Health Organization (WHO) guidelines advocate that older adults undergo 150 min of physical activity (PA) each week, performed in at least 10-min bouts [4]. Despite this, people living in nursing homes spend the majority of their time inactive [5]. A large, observational study conducted in The Netherlands reported that nursing home residents can spend 89–92% of their waking hours in sitting or lying positions [6].

A recent Cochrane review concluded that PA improves short-term function and is safe among older adults of long-term care [7]. However, the optimum contents of a PA programme or how best to implement it remain unknown [7]. Previous research has typically delivered PA programmes through exercise classes [8, 9]. While demonstrating small improvements in health outcomes, this approach can be time-consuming and resource-intensive, requiring extra equipment and specialist staff [10, 11]. As such, the sustainability of PA programmes in nursing homes has been highlighted as a particular challenge [7]. Randomised controlled trials (RCTs) assessing feasible ways to increase PA levels in nursing homes are needed, especially if long-term uptake is intended. Furthermore, to date there is limited economic evidence supporting PA programmes in nursing homes, which necessitates more cost-effectiveness evaluations to be included in trials [7].

Few studies in nursing homes have attempted to increase PA levels by embedding additional functional activities into the resident’s daily routine [12]. A person-centred programme of progressive repetitions of activities of daily living has been shown to increase the ability of older adults to perform these activities independently [13], which may provide a means of encouraging regular physical activity. Furthermore, ensuring that an intervention is perceived as relevant and meaningful by participants may be vital to its success [14, 15]. Incorporating the PA programme into the resident’s everyday routine may help to portray the relevancy of the PA programme to their lives, promoting increased participation and creating a sustainable means of increasing PA levels in the long term.

A further challenge is that older aged participants are commonly reported as having poor compliance with PA interventions [12, 16], for reasons including poor health status, poor outcome expectations, low self-efficacy, lack of support and environmental barriers [17]. Social cognitive theory (SCT) provides a framework to support participants in making positive behaviour changes [18]. This theoretical framework consists of a number of principles including: *knowledge* of health benefits arising from engaging in the positive behaviour change; a person’s *self-efficacy* that they can achieve the desired outcomes; *outcome expectations* about the expected costs and benefits of engaging in the given behaviour; personal *goals* which guide the path to behaviour change; and *perceived impediments and facilitators* to engaging in the desired behaviour change. Incorporating these constructs into PA interventions has been found to be effective in generating positive behaviour changes toward PA in the past [19, 20].

The proposed pilot feasibility study will implement a person-centred PA programme into the participant’s daily routine, based on increasing duration and repetitions of everyday functions including walking and rising from a chair. It incorporates key constructs of SCT and is monitored by nursing home staff after an initial training and support period.

### Purpose of the study

The primary aim of this pilot feasibility study is to assess the feasibility and acceptability of a PA intervention embedded into the daily lives of older adults living in nursing homes. The secondary aim is to examine the preliminary effects of this on physical mobility and quality of life, compared to participants receiving usual care. It is intended that this will facilitate the refinement of the PA programme where needed and will facilitate the development of a clear protocol for subsequent evaluation of the PA intervention in a larger, definitive RCT. The primary and secondary research questions are listed in Table 1.

**Table 1 Tab1:** Primary and secondary research questions

**Primary research questions**	
Is the intervention feasible and acceptable to staff and participants? • Is the time commitment required for staff to monitor the intervention and participants to partake in the intervention feasible? • Are there any environmental barriers to completion of the intervention? • Is the content of the intervention acceptable to participants and staff? • Do the participants adhere to the intervention and what adherence issues arise? • What are the components of usual care for participants allocated to the control group?	
Are the outcome measures feasible and acceptable to participants? • What is the required time and number of visits required to collect each outcome from participants? • Are the outcome measures acceptable to participants? • What is the level of missing data within the self-reported outcome measures? • What is the feasibility of collecting health economic data (i.e. sources used and time taken)?	
What is the required sample size for a definitive RCT? • What is the baseline score and variability of the primary outcome measure among participants? • What is the estimated effect size and variance for the primary outcome measure? • What are the recruitment and attrition rates for nursing homes and participants? Do these rates differ between the intervention and control groups?	
**Secondary research questions**	
What are the preliminary clinical outcomes and cost-effectiveness of the intervention compared to the control group? • What are the estimated outcomes of the intervention in comparison with the control group and are these sustained at 12-month follow-up? • What are the costs of the intervention in comparison to costs in the control group?	

## Methods

### Design and setting

A randomised controlled pilot feasibility study, with embedded qualitative and economic components, will be carried out. Two nursing homes will take part in the study; participants in one nursing home will receive the PA intervention and participants in the other will receive usual care. In order to avoid contamination between intervention and control groups, randomisation will take place at nursing home level [12]. The pilot feasibility study will not be an exact scale model of a definitive RCT, the difference being that follow-up outcome assessment will not be blinded as a full analysis of outcome data is not intended. However, the recruitment, randomisation, assessment and intervention conditions will be similar to a definitive RCT in order to answer the feasibility research questions. Figure 1 provides a CONSORT flow diagram displaying the movement of participants throughout the study. A schedule for enrolment, interventions and assessments is displayed in Fig. 2. The protocol adheres to the Standard Protocol Items Recommendations for Interventional Trials (SPIRIT) guidelines (Additional file 1) [21] and the SPIRIT-Patient Reported Outcomes Extension [22].

**Fig. 1 Fig1:**
[figure not shown]
CONSORT flow diagram

**Fig. 2 Fig2:**
[figure not shown]
*Schedule* of enrolment, interventions and assessments as per SPIRIT 2013

### Sites and participants

The pilot feasibility study will take place in two Irish nursing homes. Nursing home and participant eligibility criteria are outlined in Table 2.

**Table 2 Tab2:** Eligibility criteria for nursing homes and participants

Inclusion criteria	Exclusion criteria
Nursing homes	
• Registered nursing homes, either public or private. In a definitive trial, an equal number of private and public nursing homes should be allocated to each arm, in order to provide similar conditions for comparison. As this pilot feasibility study will have one nursing home in each arm, both nursing homes in the current study must be either public or private. • Located within a 30-km radius from National University of Ireland Galway (to allow the research team to provide ongoing site visits and support). • Minimum capacity of 45 residents in the nursing home (to ensure sufficient participant recruitment based on previous research [54]). • Willingness and agreement of managers to assist with the study protocol where required, including releasing relevant staff where needed and identifying residents eligible for participation.	• Voluntary nursing homes, retirement centre, day care centre, home care services or hospital. • Currently taking part in another research study which influences PA behaviour of resident. • Does not satisfy all of the above inclusion criteria.
Participants	
• Aged 65 years or over. • Can speak and understand English. • Resident in care home for at least 3 months (to allow the resident an appropriate adjustment period and time to establish daily routine). • Able to rise from a chair with armrests (with or without a walking aid) and able to walk at least 10 m (with or without a walking aid) independently or with minimal assistance. • Approval of the resident’s GP to participate (to ensure participant safety). • In the professional judgement of the key nurse caring for the resident, the resident must have the cognitive capacity to engage in the goal-setting and PA aspects of the intervention and be likely to benefit from taking part in the study. • Informed consent is obtained for participation through either (i) resident providing written informed consent or (ii) resident providing assent to participate and written informed consent obtained from the resident’s next of kin.	• Admission to nursing home for respite or end-stage terminal care. • A significant sensory impairment, physical impairment or illness that impairs their ability to participate. • Uncontrolled cardiovascular, musculoskeletal or neurological disorders.

